#### Study questions

Primary study questions:

1. What are the rates at which the population of Pakistani and Bangladeshi male smokers will set a quit date with the stop smoking services in the intervention and control areas?

2. What proportions of those setting a quit date in the intervention and control areas achieve biochemically verified prolonged abstinence from smoking at a) 4 weeks, b) 3 months and c) 6 months after the agreed quit date?

3. What is the likely degree of contamination of the intervention and control areas and the design effects that need to be taken into consideration when conducting sample size calculations for a definitive cluster randomised controlled trial?

4. What are the key components of the intervention as it develops and how do these components relate to the outcome measured by the rates of setting quit dates and abstinence among those setting quit dates?

Secondary study questions:

5. What proportion of Pakistani and Bangladeshi male smokers that book an appointment with the stop smoking service attend the initial appointment and set a quit date in the intervention and control areas?

6. What smoking cessation treatments do Pakistani and Bangladeshi men use in the intervention areas, facilitated by outreach workers, and in the control areas, without such workers?

7. What are the experiences of the services of the relevant groups in each of the trial arms and how satisfied are they?

8. What proportions of those enrolled adhere to the interventions chosen?

9. What impact, if any, are these interventions likely to have on smokeless (oral) tobacco use in these smokers?

10. What are the costs, from a health service perspective, of delivering these interventions?

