**LSSS Dataset**		

1. What is the rate at which the population of Pakistani and Bangladeshi male smokers will set a quit day with the stop smoking services in the intervention and control areas.	Recruitment rate is defined as the number of relevant population setting a quit day with the services as a fraction of all those estimated to have attempted to stop.	LSSS routine database

2. What proportions of those setting a quit day in the intervention and control areas achieve prolonged abstinence from smoking at a) 4 weeks, b) 3 months and c) 6 months after the agreed quit day?	a) Number of quits (measured by self assessment questionnaire & CO monitoring) Total number of smokers* accessing LSSS b) & c) number of quits (measured by self assessment questionnaire & CO monitoring)	a) LSSS routine database b) & c) LSSS data collected specifically for the trial

3. What is the likely degree of contamination of the intervention and control areas and the design effect that need to be considered when conducting sample size calculations for a definitive cluster randomised controlled trial?	The design effect from cluster randomisation will be calculated from the multilevel analysis. Contamination cannot be easily measured; however, we have external controls which will help indicate whether it is occurring.	

4. What are the key components of the intervention as it develops and how do these components relate to the outcome measured by the rates of setting quit dates and abstinence among those setting quit dates?	Qualitative data	Focus groups with outreach workers Observation of management meetings Shadowing Analysis of outreach worker diaries End of project interviews with outreach workers

5. What proportion of Pakistani and Bangladeshi male smokers that book an appointment with the stop smoking service attend the initial appointment and set a quit day in the intervention and control areas?	To be estimated from a sample of service providers records	SSA records LSSS Routine database

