Area number	Number of Pharmacies	Numbers using any LSSS service 06/07	Number of smokers using LSSS within area they live	Number of smokers using LSSS in other areas of randomisation	Number of smokers* using LSSS users out of study zone	Number of smokers using unidentified LSSS
1	0	7	0	0	7	0

2	1	10	1	0	9	0

3	0	29	0	8	20	1

4	3	79	41	4	32	2

5	5	155	57	2	77	19

6	4	136	43	5	84	4

7	6	98	55	0	42	1

8	2	6	0	1	5	0

9	1	2	0	0	2	0

10	0	4	0	0	3	1

11	0	8	0	5	3	0

12	0	3	0	0	3	0

13	0	11	0	8	2	1

14	1	8	0	3	5	0

15	0	2	0	0	2	0

16	0	5	0	0	5	0

*Bangladeshi or Pakistani Males aged 18 years or over

Although we will estimate the proportion of people setting a quit date, we cannot truly know the denominator, as in many cases people set multiple quit dates, hence we will consider this a rate and the 'denominator' an offset in the analysis.

Quantitative analysis will use a multilevel approach. In this model the outcome variable will be the number of individuals setting a quit date in each of the 16 randomised areas. The quasi-denominator is the estimated number wishing to quit in each area, and the log of this number will be used as an offset in a Poisson regression model. Independent variables in the model will be the group (control or intervention) and the log of the numbers setting a quit date in the previous 12 months before the trial. The randomised areas will be included in the model as a random effect, thereby allowing for the clustering inherent in the design[35]. This will be used in estimating the intra-class correlation coefficient, which in turn will determine the design effect. This is the multiplier which has to be applied to standard sample size formulae to allow for the effect of randomising at the cluster level instead of the individual level[36]. The stratification used in producing the randomisation will not be utilised in the analysis.

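### The Poisson model for uptake yields a between-area rate variance, not a unique ICC, so a design effect built on an ICC from it could mislead the sizing of the definitive trial

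*Protocol article*

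**What the plan says.** Primary question 3 (Study questions) asks for "the design effects that need to be taken into consideration when conducting sample size calculations for a definitive cluster randomised controlled trial". Table 2 answers it in one line: "The design effect from cluster randomisation will be calculated from the multilevel analysis".

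The route for uptake is set out under *Denominator for the proportion of smokers setting quit dates*:

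- Outcome: "the outcome variable will be the number of individuals setting a quit date in each of the 16 randomised areas".
- Offset: "The quasi-denominator is the estimated number wishing to quit in each area"; its logarithm enters a Poisson model.
- Covariates: trial arm and "the log of the numbers setting a quit date in the previous 12 months before the trial", with area as a random effect.
- Use of the random effect: "This will be used in estimating the intra-class correlation coefficient, which in turn will determine the design effect".
- Use of the design effect: "This is the multiplier which has to be applied to standard sample size formulae".

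The same section concedes that the true denominator is unknowable, because many people set more than one quit date, and so treats uptake as a rate. For abstinence, the following section plans a separate multilevel logistic model with a true denominator. No ICC value, design-effect formula or ICC scale is given.

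**The concern.** An ICC is the share of total variance that lies between clusters. The uptake model has one count per area and no individual-level residual. The within-area variance of a Poisson count equals its mean, so the between-area share rises with the expected count even when areas differ in their underlying rates by exactly the same relative amount. Table 3 shows baseline use from 2 to 155 men per area, so this dependence matters here.

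Sizing the definitive trial is a primary purpose of the pilot. If a figure labelled ICC is carried forward without its scale and reference count, a later team could pair it with the wrong cluster size or formula. Unequal area sizes raise a second, smaller question for any multiplier based on mean size.

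**Working it through.** The protocol states no ICC, design effect, power or sample size, so there is no figure to reproduce. Random-effect SDs, ICCs and uptake proportions below are assumptions; area sizes come from Table 3.

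**Area sizes.** 7, 10, 29, 79, 155, 136, 98, 6, 2, 4, 8, 3, 11, 8, 2, 5. Total 563, mean m = 563/16 = 35.2, median 8, SD 49.9, CV = 49.9/35.2 = 1.42. The four largest areas hold 468/563 = 83%.

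**1. ICC on the count scale.** With log-scale area variance v, let k² = exp(v) − 1. An area with expected count μ has variance μ + k²μ², so the between-area share is k²μ/(1 + k²μ).

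- SD 0.3: v = 0.09, k² = 0.0942, k = 0.31.
- μ = 2: 0.188/1.188 = 0.16.
- μ = 155: 14.60/15.60 = 0.94.
- At v = 0.05 the two values are 0.09 and 0.89; at v = 0.25 they are 0.36 and 0.98.

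One variance and one k give a different ICC for each expected count.

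**2. ICC on the proportion scale.** If p is the proportion of attempters who set a quit date, the between-area variance is k²p² and the total is about p(1 − p), so ICC = k²p/(1 − p). At k² = 0.05:

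- p = 0.02: 0.05 × 0.02/0.98 = 0.0010.
- p = 0.10: 0.05 × 0.10/0.90 = 0.0056.

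Paired with its own cluster size M = m/p, this ICC behaves well: 1 + (M − 1)ICC is 2.79 at p = 0.02 (M = 1,759) and 2.95 at p = 0.10 (M = 352), against 1 + k²m = 2.76. Mispaired, it does not. The ICC from p = 0.02 used with M = 352 gives 1 + 351 × 0.00102 = 1.36. The ICC from p = 0.10 used with M = 1,759 gives 1 + 1,758 × 0.00556 = 10.8. So the error can go either way.

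A constant proportional error in the offset, such as a wrong common quit-attempt proportion, moves only the model intercept and leaves v and k unchanged. Errors that differ between areas would enter both.

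**3. Precision.** Sixteen areas less three fixed parameters leave about 13 degrees of freedom. The chi-square 95% interval for the variance is 0.53 to 2.6 times the estimate, at best, since it ignores Poisson noise. For v = 0.09 that is about 0.048 to 0.234, or k from 0.22 to 0.51. A simulation of 200 trials with these area sizes (rate ratio exp(0.3), baseline count as offset, true v = 0.05) put the central 95% of variance estimates between 0 and 0.16.

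**4. Unequal sizes.** Three multipliers, with Table 3 counts as a proxy for quit dates set:

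- mean size: 1 + (m − 1)ICC
- size-weighted: 1 + ((1 + CV²)m − 1)ICC, where (1 + CV²)m = 106.0
- efficient weighting: Σmᵢ / Σ[mᵢ/(1 + (mᵢ − 1)ICC)]

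| Assumed ICC | Mean size | Size-weighted | Ratio to mean size | Efficient | Ratio to mean size |
|---|---|---|---|---|---|
| 0.001 | 1.03 | 1.11 | 1.07 | 1.10 | 1.07 |
| 0.01 | 1.34 | 2.05 | 1.53 | 1.89 | 1.41 |
| 0.02 | 1.68 | 3.10 | 1.84 | 2.61 | 1.55 |
| 0.05 | 2.71 | 6.25 | 2.31 | 4.31 | 1.59 |

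**The case against.** The strongest reply is that an ICC can be had. Reach is defined as a proportion of those attempting to quit, and on that scale the same random effect gives an approximate ICC. With matching p and cluster size, its design effect (2.79 to 2.95) is close to the rate-based 2.76. This stands as far as it goes, so a reader should not infer that no ICC can exist for uptake. But the ICC is usable only together with p, which rests on an estimated denominator and a quit-attempt proportion borrowed from the general population. The quantity k does not need p.

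A reader might also infer that the plan commits to a single design effect of the form 1 + (m − 1)ICC. It does not. The formula is never written, question 3 speaks of design effects in the plural, and abstinence has its own logistic model from which a conventional ICC can be obtained. An article may leave the formula to a fuller document, so its absence is no fault.

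Nor do the documents support saying that the usual multiplier is far too small or that the definitive trial would be mis-sized. The shortfall depends on an ICC they do not give. The planned multilevel models approximate efficient weighting, for which the ratios are smaller. The definitive trial's area sizes are not fixed here, so Table 3's CV need not carry over.

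Finally, imprecision is common to any pilot with 16 clusters. That is true and is no error in the text; it is a reason to carry the interval forward.

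**Conclusion.** The point holds for uptake. The plan names an ICC as the output of a model that delivers a between-area variance of log rates, and makes that ICC the basis of the design effect. The count-scale ICC is not unique: 0.16 to 0.94 across the Table 3 range at an assumed SD of 0.3. The proportion-scale ICC varies more than fivefold (0.0010 to 0.0056) over p from 0.02 to 0.10 at k² = 0.05. A figure reported without its scale could mislead the later sample size in either direction.

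No information is lost, because the planned model already estimates the variance from which k follows.

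On unequal sizes the conclusion is conditional: if a mean-size multiplier were used with clusters like those in Table 3, it would be too small by a factor of about 1.07 at ICC 0.001, and by 1.6 (efficient weighting) to 2.3 (size-weighted) at ICC 0.05. These ICCs are assumptions, and the protocol does not say it will use that multiplier.

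**What to change.** - **Uptake.** Replace the ICC by the log-scale area variance v and k = sqrt(exp(v) − 1), with a 95% interval, noting that both are conditional on the baseline count. Size the definitive trial on rates, taking the variance of an area's rate λ with denominator y as λ/y + k²λ². Check the upper part of the interval for k as well as the point estimate. If an ICC is also quoted, state its scale and the p or expected count it assumes.
- **Abstinence.** Report the ICC from the logistic model with its interval and state its scale.
- **Design effect.** As a precaution, use a form that allows for unequal cluster sizes, with the size variation expected in the definitive trial, and name the weighting assumed.

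This needs no new data and no change to the fitted models, only to the analysis and reporting text. The downside is a less favourable and openly uncertain design effect.

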### Randomisation

We will use census super output areas (SOAs) as the unit of allocation[30]. In order to define these communities, initially all those SOAs within the study area with a combined Bangladeshi and Pakistani population of more than 10% will be identified and then mapped at ward level, enabling the street boundaries of each SOA to be seen. Contiguous SOAs will then be aggregated into natural communities (i.e. areas where people live, work, shop etc) using the local knowledge of the LSSS managers and advisors. SOAs in which more than 30% of the population are Pakistani and Bangladeshi will be considered to be high-density areas, while SOAs with 10–29% of the population being from these groups will be defined as low-density areas.

A total of 16 aggregated areas, sufficiently geographically dispersed, will be created to be randomised; there will thus be eight SOAs in each arm. For the randomisation, we will stratify, firstly by the proportion of Pakistani and Bangladeshi residents and secondly by absolute population size, to create eight areas that include high target population density and eight that are low-density areas. The high density areas will be further subdivided into those areas with target populations of Bangladeshi and Pakistani men above and below 10,000. The low density areas will be further subdivided into those areas with target populations above and below 300. Table 1 shows how the areas will be allocated. Randomisation will be undertaken by the study statistician who has no knowledge of the geographical areas using permuted blocks. Within each of the four strata, two areas will be randomly allocated to 'control' and two to 'intervention' arms. Maps of the final areas and their allocation to the two study arms are shown in Figures 1 and 2.

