#### Definition and modelling of abstinence rates

The quit rate is defined as the proportion of people achieving abstinence, with a denominator of all those who attended the service and set a quit date. Quitting is defined as prolonged abstinence, which is defined as allowing lapses during the first two weeks of the quit process measured according to the Russell standard[37]. Self-reporting is substantiated by biochemical validation using expired carbon monoxide (less than 10 parts per million)[38].

The modelling will follow the same approach as described above for calculation of usage rates, except that we will have a true denominator. We will therefore use multilevel logistic regression models rather than Poisson models.

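### The abstinence ICC from 16 very unequal areas is too imprecise, in both directions, for one estimate to fix the definitive trial's design effect

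*Protocol article*

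**What the plan says.** Primary study question 3 asks for "the design effects that need to be taken into consideration when conducting sample size calculations for a definitive cluster randomised controlled trial". The Table 2 entry for that question says: "The design effect from cluster randomisation will be calculated from the multilevel analysis".

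The method is under the heading on the denominator for the proportion of smokers setting quit dates. The uptake outcome is "the number of individuals setting a quit date in each of the 16 randomised areas", and area enters a Poisson model as a random effect. On that effect the text says: "This will be used in estimating the intra-class correlation coefficient, which in turn will determine the design effect". It then describes the design effect: "This is the multiplier which has to be applied to standard sample size formulae".

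The section on defining and modelling abstinence rates carries this over: "The modelling will follow the same approach as described above for calculation of usage rates, except that we will have a true denominator". Multilevel logistic regression replaces the Poisson model. The denominator is everyone who set a quit date, and men lost to follow-up count as smoking, so losses do not shrink the areas.

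The article gives no value for the ICC or the design effect, and mentions no interval, range or upper limit for either.

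**The concern.** An ICC is a well-defined quantity for abstinence, but it rests on a between-area variance. A variance estimated from few, very unequal areas has a wide and skewed sampling distribution, with a pile-up at zero. If one estimate fixes the multiplier, all of that error passes into the sample size of the definitive trial.

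Sizing that trial is one of the pilot's stated purposes. A design effect that is too low leaves the definitive trial short of power. One that is too high makes it needlessly large, or makes it look infeasible.

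There is a smaller point of the same kind. The uptake model includes the log of the previous year's count as a covariate. If the abstinence model has a similar covariate, its ICC is a residual one, and it should be paired only with a sample size formula that assumes the same adjustment. The article does not say which ICC is meant.

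**Working it through.** The protocol states no sample size, power, ICC or design effect, so there is no figure to reproduce. The check asks how well an abstinence ICC can be estimated from areas of the sizes shown.

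**Inputs from the protocol**
- Area sizes, from the Table 3 column "Numbers using any LSSS service 06/07": 7, 10, 29, 79, 155, 136, 98, 6, 2, 4, 8, 3, 11, 8, 2, 5.
- Allocation: "Within each of the four strata, two areas will be randomly allocated to 'control' and two to 'intervention' arms".

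**Assumed inputs**
- True ICC from 0.01 to 0.10; abstinence of 40%, and of 10% as a check.
- Definitive area size of 35, the Table 3 mean: 563/16 = 35.2.
- Stratum membership, set by ranking the areas by size.

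**Effective number of clusters**
- Total 563, median 8. Eleven areas hold 2 to 11 men each. The four largest hold 79 + 155 + 136 + 98 = 468, and 468/563 = 83%.
- Σn² = 59,699, so (Σn)²/Σn² = 316,969/59,699 = 5.3.

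**Design effect**
- DE = 1 + (35 − 1) × ICC.
- True values: 1.34 at ICC 0.01, 1.68 at 0.02, 2.70 at 0.05 and 4.40 at 0.10.

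**Simulation**
- 20,000 pilots per setting, with beta-binomial outcomes at the Table 3 sizes.
- Two of four areas to each arm in each stratum. ANOVA ICC within arms, set to 0 if negative.
- Results at 40% abstinence. Runs with different random seeds agree to about one percentage point.

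| True ICC | True DE | ICC estimate zero | ICC below truth | DE below 80% of truth | DE above 125% of truth | DE 5th–95th percentile |
|---|---|---|---|---|---|---|
| 0.01 | 1.34 | 32–33% | 55% | 37% | 26% | 1.0–2.5 |
| 0.02 | 1.68 | 20–21% | 56–57% | 39% | 25–26% | 1.0–3.1 or 3.2 |
| 0.05 | 2.70 | 6–7% | 58–59% | 41% | 25% | 1.0–5.3 |
| 0.10 | 4.40 | 1% | 59% | 42% | 26% | 1.5–8.8 |

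- At ICC 0.02 the lower mark is 0.80 × 1.68 = 1.34, and the upper mark is 1.25 × 1.68 = 2.10.
- The mean estimated DE at ICC 0.02 is 1.72–1.73 against 1.68, so the estimate is not low on average.
- At 10% abstinence, zeros occur in 38%, 25–26%, 9–10% and 3% of pilots at the four ICCs.

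**Check with the planned type of model**
- A random-intercept logistic model with an arm term was fitted by maximum likelihood at 10%, 20% and 40% abstinence, 800 runs per setting. The ICC was approximated on the proportion scale as s²p(1−p)/(s²p(1−p)+1).
- Zeros occurred in 54–60%, 37–39% and 18–21% of runs at ICC 0.01, 0.02 and 0.05. Between 70% and 82% of estimates fell below the truth.
- With every area size doubled (400 runs per setting), zeros still occurred in 38–46%, 19–25% and 7–9% of runs.

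**What a zero estimate would cost**
- Illustration with assumed rates of 10% versus 15%, two-sided alpha 0.05 and 80% power: 686 per arm if DE = 1.
- With DE = 1 + 34.2 × 0.02 = 1.684, the need is 686 × 1.684 = 1,156 per arm, rounded up. Recruiting only 686 per arm leaves 58% power.

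**The case against.** The strongest reply is that the article nowhere says a point estimate will be used and nowhere rules out an interval. The key sentence can be read as a definition, since a design effect is a function of an ICC. Elsewhere the article says only that the data will inform sample size calculations, and the form of reporting may be settled in a full analysis plan. This has weight: the missing interval alone would be no finding. What stands is that the published wording lets the estimated ICC settle the multiplier for a primary question, and Table 3 shows that it cannot.

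The sentence also sits in the uptake paragraph, and the article links definitive-trial sizing to reach. It applies to abstinence only because the abstinence section adopts the same approach and question 3 speaks of design effects in the plural. That link is reasonable but inferred.

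A reader might infer that the rule would under-size the definitive trial, or that the ICC will often come out at zero. Neither is supported as a general statement. In the main simulation about a quarter of pilots overstate the design effect by more than 25%. The logistic fits fall low more often, but their upper tail is also long. Frequent zeros depend on an assumed ICC of about 0.02 or less, and they are rare at 0.10.

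The mismatch between an adjusted ICC and standard formulae has no computed size here. No baseline covariate is specified for abstinence, so this is a request for clarity and not a demonstrated error.

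**Conclusion.** The concern holds as one of imprecision in both directions, somewhat more often low. At an assumed ICC of 0.02 and 40% abstinence, pilots of this shape return design effects from 1.0 to about 3.1–3.2 where 1.68 is right. About two in five fall below 80% of the true value and about one in four exceed 125% of it. About a fifth give an ICC of zero; the share is about a third at ICC 0.01, about 6% at 0.05 and about 1% at 0.10.

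These figures rest on the assumed ICC, abstinence rate, definitive area size and strata, and on baseline-year counts standing in for intervention-year counts. They use an ANOVA estimator, whereas the plan is for a logistic model, which gave more zeros. The spread is wide at every ICC examined. The pilot's own comparison of arms is not affected; what question 3 can conclude is.

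**What to change.** In the quantitative analysis text and the abstinence modelling section, replace the statement that the ICC settles the design effect with a rule on these lines:

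- Report the abstinence ICC with a 95% interval.
- Give the design effect as a range over that interval, and check the definitive trial's size at a conservative upper value stated in advance. The choice of upper value is a convention; the need is to fix it before the estimate is seen.
- Do not take an ICC estimate of zero as a design effect of 1.
- State whether the ICC is adjusted for a baseline covariate, and use it only with a sample size formula that assumes the same adjustment.

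No new data are needed. The article says the intervention period has ended and analysis is under way, so only the analysis rule and the reporting change. The cost is a less favourable and less exact design effect for planning the definitive trial.

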#### Denominator for the proportion of smokers setting quit dates

Our overall aim is to develop and refine the intervention, to pilot it, and have the data needed to inform sample size calculations for a definitive trial evaluating these interventions. In order to perform sample size calculations for a future trial, we aim to assess the reach of the interventions in attracting smokers wanting to quit. For the purposes of this study, reach has been defined as the proportion of each relevant ethnic group setting a quit date using the stop smoking service, with the denominator for this being all those of relevant ethnic group attempting to quit during the same period. We are estimating this latter number as it cannot be directly measured. We have searched a variety of sources to give information on the proportion of each ethnic group that attempted to quit in the past year and these data are not available. No local survey can truly randomly survey Pakistani and Bangladeshi populations because there is no publicly available local sampling frame that records ethnicity. Consequently, we will use the Smoking Toolkit Study to provide relevant data on the proportion of people that attempted to quit in the past year for the general population and assume that this figure is approximately the same in Pakistani or Bangladeshi men[34].

Stop smoking services routinely record information about each of their patients, including their age, gender, ethnic group, type of service used, medication used and outcome. This will be used to give both a before and after measure of the use of the service by the relevant groups (i.e. males of Pakistani and Bangladeshi ethnic group). Thus, we will have, for each area, the rate of use of the service for 12 months prior to the intervention that will serve as a baseline variable in the analysis (see Table 3). The after measure will be the same data collected for the 12 months during which the outreach workers are active. These data will be supplied anonymously from BEN and HoBt PCTs and this does not rely on data collection developed for the study. As noted above, the before-after design will allow control for intrinsic variability between areas. As such there will be no attempt to assess baseline balance between the intervention and control areas.

**Table 3 T3:** Use of LSSS by randomisation area residents for the baseline period (1st November 2006 – 31^st ^October 2007)

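### The analysis sets aside the four randomisation strata without a reason, which can inflate the standard error and the design effect if strata still predict uptake

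*Protocol article*

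**What the plan says.** In the Protocol article, the Randomisation section sets the number of units, "A total of 16 aggregated areas, sufficiently geographically dispersed, will be created to be randomised", and the factors: "we will stratify, firstly by the proportion of Pakistani and Bangladeshi residents and secondly by absolute population size". Allocation is balanced in each stratum: "Within each of the four strata, two areas will be randomly allocated to 'control' and two to 'intervention' arms". Table 1 repeats the scheme (high density below or above 10,000; low density below or above 300).

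The analysis is in the section on the denominator for smokers setting quit dates. It is a Poisson model of each area's count. For the estimated number wishing to quit, "the log of this number will be used as an offset in a Poisson regression model". The covariates are stated: "Independent variables in the model will be the group (control or intervention) and the log of the numbers setting a quit date" in the year before. "The randomised areas will be included in the model as a random effect", and that random effect supplies the intra-class correlation and design effect. The paragraph ends: "The stratification used in producing the randomisation will not be utilised in the analysis".

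The abstinence section says its models follow the same approach, so both quantitative primary outcomes appear to inherit the rule. The text after Table 1 relies on stratification to balance key confounders and calls such confounders possible effect-modifiers. No alpha, power, target effect or expected intra-class correlation is stated.

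**The concern.** With two areas per arm in every stratum, differences between strata cancel from the arm comparison. A model without strata leaves whatever the offset and baseline covariate do not explain of those differences in the residual area variance. The estimated standard error then describes a less precise design than the one used.

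Two things are at stake. One is the precision of the arm comparison. The other matters more in a pilot: study question 3 asks for the design effect to use in planning a definitive trial, and that figure comes from the same area variance. If the later trial stratifies in the same way, it would be sized on variance that its own design removes.

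**Working it through.** The plan states no figure that could be reproduced. The checks below rest on stated assumptions and concern the quit-date rate only.

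**1. Area-level break-even.** Inputs: 16 areas, 4 strata of 4, 2:2 allocation (Randomisation section), one covariate. Assumed: two-sided 5%, t reference. Let ρ be the share of residual area variance that lies between strata.

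- Residual df without strata: 16 − 3 = 13, t = 2.160. With strata: 13 − 3 = 10, t = 2.228. Ratio 2.228/2.160 = 1.031.
- Of the 13 df, 3 belong to strata, with expected mean square σw² + 4σb². Ignoring the covariate, the residual mean square relative to σw² is about 1 + (12/13)·ρ/(1 − ρ).
- At ρ = 0.3: 1 + 0.923 × 0.429 = 1.40. This is the inflation of the area variance.
- Break-even is where the inflation equals 1.031² = 1.064: ρ/(1 − ρ) = 0.064 × 13/12 = 0.069, so ρ ≈ 0.065.

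Simulation of the same setting (6,000 trials per row):

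| ρ | CI half-width, with/without strata | Power without → with | Type I error without strata |
|---|---|---|---|
| 0 | 1.04 | 76.4% → 74.0% | 5.0% |
| 0.05 | 1.01 | 77.5% → 76.1% | 4.4% |
| 0.10 | 0.99 | 77.6% → 77.8% | 4.3% |
| 0.30 | 0.89 | 80.9% → 86.1% | 3.0% |
| 0.50 | 0.78 | 83.5% → 95.0% | 1.6% |

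This agrees with the formula: the break-even lies at ρ of about 0.05 to 0.10.

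**2. Permutation tests on Table 3 sizes.** Assumed: strata by rank of the Table 3 count, rate ratio 1.5. Within-stratum allocations: C(4,2)⁴ = 6⁴ = 1,296. Unrestricted: C(16,8) = 12,870. Power, within-stratum versus unrestricted, in two runs:

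| SD of stratum change (log scale) | Run A | Run B |
|---|---|---|
| 0 | 38% v 39% | 53% v 57% |
| 0.3 | 53% v 39% | 52% v 35% |
| 0.5 | 51% v 24% | 49% v 20% |

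Run A used 400 trials per setting (Monte Carlo error up to √(0.25/400) = 2.5 points). Levels differ between the runs, so only the direction should be read. The within-stratum test held about 4 to 6% type I error; the unrestricted test rejected 0.75% at rate ratio 1 in run A.

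**3. The planned covariates, fitted as a negative binomial with a t reference.** Assumed: stratum populations 14,000/5,000/500/200, rate ratio 1.6, area SD 0.15 or 0.30, 1,000 trials per setting.

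| Rates across strata | Baseline term | Power without → with strata (SD 0.15; SD 0.30) |
|---|---|---|
| Equal | log count | 53.7% → 59.4%; 42.1% → 43.7% |
| Differing (Table 3 ranks) | log count | 12.7% → 59.8%; 12.6% → 42.6% |
| Equal | log rate | 72.9% → 70.9%; 47.6% → 47.4% |
| Differing | log rate | 65.5% → 68.4%; 44.9% → 45.4% |

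In the second row, type I error without strata was 0.1% and 0.7%; with strata it was 7.7% and 7.0%, so the gain is partly one of test size. With equal rates and a log count at SD 0.15, the unstratified standard error was not too large (mean 0.212, empirical SD 0.223, under no effect). The large loss therefore needs both strongly differing rates and a log count beside the offset. The same section elsewhere describes "the rate of use of the service for 12 months prior to the intervention that will serve as a baseline variable in the analysis"; with a log rate, strata change power by only −2 to +3 points.

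**4. Maximum likelihood with Wald z intervals.** For a Poisson-normal mixed model on Table 3 sizes (250 fits per setting), type I error was 10 to 15% without strata and 16 to 26% with stratum terms added. A separate unstratified fit (120 trials per setting, within-stratum SD 0.1, offset proportional to the Table 3 count) gave mean SE 0.108 against empirical SD 0.136 at stratum SD 0.3 (type I error 14%), and 0.132 against 0.163 at SD 0.5 (19%).

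**The case against.** The strongest reply is that the plan already adjusts. The offset removes size, the baseline count removes much of the level, and the protocol relies on its before-after comparison to deal with variability between areas. Large differences in population between strata concern level and do not show that change differs by stratum. With 563 baseline users, 468 of them (83%) in four areas and 11 areas with 11 or fewer, saving 3 of 13 df is defensible. The study is a pilot with no stated power or test. The definitive trial is described only as multi-centre and cluster randomised; if it were unstratified, the larger variance would be the relevant one.

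Most of this stands. It makes the harm conditional and weakens the power argument. It does not justify the rule: the omission is fixed without a reason, the stratum SDs that would make it harmless are as unknown as those that would make it costly, and baseline counts of 2 to 11 are noisy adjusters.

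A reader might infer that ignoring strata necessarily makes the planned intervals too wide. The documents do not support that. They name neither the fitting nor the test method, and an ordinary Wald fit with 16 areas can give intervals that are too narrow, with or without strata.

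**Conclusion.** The point holds conditionally: should-fix, not must-fix. The analysis departs from the randomisation scheme by an explicit, unexplained rule. Where strata hold more than about 5 to 10% of residual area variance after adjustment, and the reference distribution is valid for few clusters, the standard error is too large and power is lost: about 5 points at 30% and 11 to 12 points at 50% in the area-level model. The area variance passed to the definitive trial is about 1.4 times the within-stratum value at 30%, an overstatement only if that trial stratifies similarly. Where strata add nothing, ignoring them is free or gains about 1 to 4 points.

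The actual loss cannot be computed, because neither stratum rates nor the assignment of areas to strata is given. The drop from 59.8% to 12.7% power should not be read as an estimate for this trial; it rests on assumed rates and on the log-count form of the baseline term.

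**What to change.** Replace the sentence with: *The analysis will account for the four randomisation strata.* Give stratum-adjusted estimates, and take p-values and confidence intervals from permutation of areas within strata (1,296 allocations) or from another method suited to 16 clusters. Do not merely add three stratum terms to a Wald z analysis, which can make the intervals too narrow. Report the area variance and the design effect with and without strata, so that the definitive trial can use the one that matches its design.

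The switch of arms described under Protocol amendments leaves this permutation scheme usable for a two-sided statistic if the arms were exchanged as a whole. The protocol should say so.

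Cost: no new data; 3 of about 13 area-level degrees of freedom; and a few points of power if the strata prove uninformative. The intervention period had ended and analysis was under way at publication, so the change should be made and dated before outcomes are compared by arm. If that point has passed, report it as a labelled sensitivity analysis beside the planned one.
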